### Intervention

The GP Toolkit comprises two resources. The first resource will be a Needs Assessment Tool - Caregivers (NAT-C), which is a two-page needs assessment tool provided to intervention group caregiver participants to self-assess their unmet needs across a number of domains, including physical and psychological well-being, as well as spiritual, existential, social, financial and legal concerns. The tool can be completed by the caregiver or by the GP and caregiver together. The development of the NAT-C was based on a comprehensive literature review and was modelled on a pre-existing needs assessment tool, the Needs Assessment Tool: Progressive Disease - Cancer (NAT: PD-C), which has been extensively pilot-tested and validated [23,24]. Note that the NAT-C is not a validated measure of needs, rather a checklist that enables the content of the consultation to be focussed quickly on relevant matters.

The second resource is a folder of complementary materials for GPs, outlining the types of problems that might arise for caregivers and linking GPs to evidence--based information and other suggested strategies and resources that might help address problems identified at the consultation. These strategies include utilising the relevant EPC options, and accompanying documentation to facilitate their use. The resource materials will include brief descriptions and contact details of commonly used information services, such as Palliative Care Australia and State-based Cancer Council hotline resources for patients and caregivers. This resource will be supplied to GPs in a folder of indexed sections as well as in electronic format on a CD.

### Procedure

All participating caregivers will be mailed a copy of the CATI survey questions on entry to the study, for reference during the CATI phone calls. These interviews will be conducted by trained and experienced personnel, who will be blinded to the group assignment of participants. CATI data will be collected from control and intervention group caregivers at the same four time points. Baseline CATIs occur before the intervention group caregivers consult the GP. Apart from these interviews, the control group will not be subject to any further intervention from the project.

Intervention group caregivers will also receive a triplicate copy of the NAT-C, with a covering letter to explain the purpose of the NAT-C, to ask caregivers to complete this form and to attend their GP with the completed form as soon as practicable to discuss their needs, with a target of between one and two weeks to allow the GP to first receive an educational visit. At three months following entry into the study, intervention group caregivers will be asked to complete a second NAT-C and discuss it with their GP, to identify and deal with changing needs as the patient's disease progresses.

GPs of the intervention caregivers will be individually visited once by research staff as soon as possible after participant recruitment and allocation to the intervention group, to explain the use of all elements of the GP Toolkit. The research team will follow up GPs by phone to provide any further support required and to ensure the intervention is fully implemented. The frequency of these calls will be tailored to the needs of individual GPs. GPs with more than one caregiver participant will receive a visit only after the first participant is recruited. GPs will be encouraged to use the NAT-C as a guide to discussing the needs nominated by the caregiver, and to planning a course of action. There are no prescribed interventions for given identified needs. Any agreed actions are entirely up to the treating doctor and the caregiver.

Intervention patients who choose not to complete a NAT-C will still be encouraged to visit their GP, who may also choose to use the copy of the NAT-C in the GP Toolkit to guide the discussion, or not. The GP and the caregiver may choose to complete the NAT-C together.

### Outcome measures

A CATI survey will be conducted with caregivers at baseline (t0), one month (t1), three months (t2) and six months (t3) after their recruitment into the study. Demographic characteristics and aspects of the caregiving role will be assessed using questions previously utilised in a trial of health professional investigating the uptake of the *Palliative Care Needs Assessment Guidelines *[25] and NAT: PD-C [23,24].

The outcome variables to be assessed will include: unmet needs, anxiety, depression, QoL, coping style and financial impact. All of these will be evaluated using the selected measures detailed below, which have demonstrated reliability and validity.

#### Unmet needs

The Supportive Care Needs Survey - Partners and Caregivers (SCNS-P&C44) is a 44 item measure, which will be used to assess caregivers' level of unmet needs across the following domains: *Health Care Service Needs*, *Psychological and Emotional Needs*, *Work and Social Needs *and *Information Needs *[26].

#### Anxiety and depression

The Hospital Anxiety and Depression Scale (HADS), a 14-item survey with scoring that classifies participants' anxiety and depression levels as low, borderline or clinically significant [27], will be used to assess caregivers' level of anxiety and depression.

#### Quality of Life

QoL will be assessed using the SF-12v2, a 12-item measure evaluating QoL across 8 health concepts: physical functioning, role limitations because of physical health problems, bodily pain, general health perceptions, vitality (energy/fatigue), social functioning, role limitations because of emotional problems, and general mental health [28].

#### Coping

The Brief COPE will be used to assess coping strategies used by caregivers participating in the study. The Brief COPE is a 28-item survey consisting of 14 scales (2 items per scale): self-distraction, active coping, denial, substance use, use of emotional support, use of instrumental support, behavioural disengagement, venting, positive reframing, planning, humour, acceptance, religion, and self-blame [29].

### Sample size and statistical analysis

A sample of 520 caregivers will be recruited. This number has been estimated to account for approximately 25% attrition over the study period, so that 400 will complete the study, 200 in each group. This will involve approximately 330 GPs in total. The primary outcome measure is levels of unmet needs as measured by the SCNS-P&C. Based on previous research [24] utilising the standard deviations for each of the domains for the patient version of the SCNS [30-32] (between 15 to 24), and using a 5% significance level, having a minimum of 200 caregivers in each of the two comparison groups will give the study 80% power to detect a difference of between 4.2% and 6.7% in each of the SCNS-P&C domains for caregivers. It will also be able to detect a difference of between 0.9 and 1.4 units in anxiety and depression scores (HADS [7]), the secondary outcome measures.

Longitudinal analyses of the endpoints over time will be undertaken using generalised estimating equations (GEEs) [33]. GEEs are an extension to generalized linear models (GLMs). Linear regression models can only analyse the data cross-sectionally, however the 'extension' component of the GEE model allows for the analysis of the data longitudinally, thus reflecting the relationship between the longitudinal development of the dependent variable and the longitudinal development of the independent variables over time. An indicator variable identifying the control/intervention groups, socio-demographic factors and other confounding variables will be included in the GEE models. Analyses will be conducted on an intention to treat basis.

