### Study aims and hypotheses

The overall aims of the proposed study are to:

1. Use randomized controlled methods to assess the efficacy of the systematic utilisation of a GP Toolkit in reducing caregivers' reported number and level of unmet needs.

2. Evaluate the acceptability of the intervention for GPs and caregivers.

For the proposed study it is hypothesised that the number and levels of unmet needs of caregivers of patients with advanced cancer will be significantly lower in caregivers whose needs are systematically assessed using a needs assessment tool and then addressed by their GP, compared with caregivers receiving usual care.

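### The sample size gives 80% power in each of four primary SCNS-P&C domains at an unadjusted 5%; if any one significant domain counts as success, the false-positive chance is up to about 19%

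*Protocol article*

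**What the plan says.** Under Sample size and statistical analysis, the protocol article states: "The primary outcome measure is levels of unmet needs as measured by the SCNS-P&C". The Unmet needs section says that the SCNS-P&C44 "is a 44 item measure, which will be used to assess caregivers' level of unmet needs across the following domains", and lists four: health care service, psychological and emotional, work and social, and information needs. It mentions no total score and singles out no domain.

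The sample size is set by "using a 5% significance level, having a minimum of 200 caregivers in each of the two comparison groups", which is said to give "80% power to detect a difference of between 4.2% and 6.7% in each of the SCNS-P&C domains for caregivers". The standard deviations are 15 to 24, borrowed from the patient version of the instrument. Of the 520 caregivers recruited, the plan expects attrition "so that 400 will complete the study, 200 in each group".

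The hypothesis, under Study aims and hypotheses, is wider than the primary outcome. It says that "the number and levels of unmet needs of caregivers of patients with advanced cancer will be significantly lower" in the intervention group. The first aim also covers both number and level.

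The analysis paragraph plans longitudinal GEE models with a group indicator. It does not say how results from the four domains combine into a conclusion.

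**The concern.** With four primary comparisons each judged at 5%, the error rate that matters is the one attached to the trial's conclusion, namely whether the GP Toolkit reduces unmet needs. Nothing in the article stops one significant domain out of four from being reported as confirmation. In that case 5% is not the error rate of the claim.

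The stated power has the matching problem. It is correct for a single domain tested alone at 5%. It no longer holds at the stated differences once the error is shared across domains, or once all domains are required.

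The hypothesis adds a second metric, the number of needs, which neither the primary outcome nor the power statement covers. That gives a further possible route to a positive claim.

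**Working it through.** **Inputs from the protocol article.** 200 completers per group; 5% significance level; 80% power; SD 15 to 24; stated differences 4.2 to 6.7, read as points on the same scale as the SDs; four domains. The correlation between domain test statistics is not given, so it is varied from 0 to 0.9 as an assumption.

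**1. Reproduce the stated differences.** With n per group, the detectable difference is (z for 1 − α/2 + z for power) × SD × √(2/n). Here √(2/200) = 0.1, and for two-sided 5% and 80% power the multiplier is 1.960 + 0.842 = 2.802.
- SD 15: 2.802 × 15 × 0.1 = 4.20.
- SD 24: 2.802 × 24 × 0.1 = 6.72.

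Both match. Solved for n, the stated differences need 201 and 202 per group at two-sided 5%. A one-sided 5% would need only 158 and 159. The calculation therefore used the full two-sided 5% for each domain, with nothing set aside for there being four.

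**2. Error if any one domain suffices.** For k independent tests at 5%, the chance of at least one false positive is 1 − 0.95^k. For correlated tests it was simulated with equally correlated normal test statistics (2 million draws).

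| Correlation | Four domains | Four domains plus number of needs |
|---|---|---|
| 0 | 1 − 0.95^4 = 18.5% | 1 − 0.95^5 = 22.6% |
| 0.3 | 17.4% | 20.9% |
| 0.5 | 15.6% | 18.2% |
| 0.7 | 13.0% | 14.8% |
| 0.9 | 9.4% | 10.1% |

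As the correlation approaches 1, both columns fall to 5%. The first column counts a significant result in either direction. Counting only results that favour the intervention, the four-domain figures are 9.6% at correlation 0, 7.8% at 0.5 and 6.5% at 0.7, against a nominal 2.5%.

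**3. Power if all four domains are required.** The error is then at most 5%. If every domain truly has its detectable difference, the power to reach significance in all four is 0.80^4 = 41% under independence. Simulation gives 56% at correlation 0.5, 62% at 0.7 and 70% at 0.9.

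**4. Power and detectable difference with the error shared.** Bonferroni, which is also the first Holm step, uses 0.05/4 = 0.0125 per domain, so z = 2.498 and the multiplier is 2.498 + 0.842 = 3.339.
- Detectable difference with 200 per group: 3.339 × 15 × 0.1 = 5.0 and 3.339 × 24 × 0.1 = 8.0.
- Power at the stated differences: Φ(4.2/1.5 − 2.498) = Φ(0.302) = 62%, and Φ(6.7/2.4 − 2.498) = Φ(0.294) = 62%.
- Completers needed to restore 80% at the stated differences: 285 to 287 per group.

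Like the article's own calculation, these figures are for a comparison at one visit without baseline adjustment.

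**The case against.** The strongest reply is that the article names a single primary measure and nowhere says that the four domains are separate routes to success. The per-domain wording appears only in the power statement, and that statement is arithmetically right. The success rule, the primary contrast and any multiplicity procedure are commonly left to a statistical analysis plan, which is not shown. All of that stands, and it makes the error figures conditional.

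It does not remove the point. The number of completers is fixed on this page, and it was derived with no allowance for four comparisons. A later plan could add an adjustment, but the single-visit detectable differences printed here would then no longer carry 80% power. The mismatch between a hypothesis on number and levels and a primary outcome on levels alone also lies within the article itself.

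Two stronger readings are tempting and are not supported. First, a reader might infer that the trial's error rate simply is 13% to 19%. That range needs an any-domain success rule and correlations between 0 and 0.7, and the article gives neither. Second, a reader might multiply four domains by three follow-up visits and infer 1 − 0.95^12 = 46%. The article describes longitudinal GEE models with a group indicator, not separate tests at each visit, and repeated scores from one caregiver are not independent.

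**Conclusion.** The point holds in conditional form and should be fixed. The primary outcome has four domains with no lead domain or summary score, and the sample size spends the full two-sided 5% on each.

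If any one significant domain counts as success, the false-positive chance is at most about 19%, falling with the correlation between domains to about 9% at 0.9. It is up to about 23% if the number of needs is a fifth test. If all four domains are required, the error is controlled but power falls short of 80%.

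The power figures are for a single visit without baseline adjustment. The longitudinal models may do better by an amount that cannot be computed from the article.

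**What to change.** Choose one of two routes before any unblinded analysis:
- control error across the four domains with Holm's procedure, applied to one pre-specified group contrast per domain from the GEE model; or
- name one primary score and treat the remaining domain results as secondary.

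Which contrast to use is for the trial team to decide. An average over follow-up visits is one possibility, but it could dilute an effect that the Discussion expects to become more evident over six months.

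In either case, make the number of unmet needs a secondary outcome and reword the aim and hypothesis to match the primary outcome. If the first route is taken, restate the detectable difference at the Bonferroni or first Holm step as 5.0 to 8.0 points with 200 per group (power about 62% at 4.2 to 6.7), and say that this is before any gain from baseline adjustment or repeated measures.

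The change is to wording only and needs no new data. Its cost under the first route is a less favourable stated detectable difference.

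### The listed GEE terms name neither the baseline SCNS-P&C score nor a group-by-visit term, and the role of the pre-intervention t0 survey is left open; settling both costs nothing and protects effect size and precision

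*Protocol article*

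**What the plan says.** All points are from the Protocol article.

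- **Model** (Sample size and statistical analysis). The endpoints are to be analysed over time by GEE. Of the terms it says: "An indicator variable identifying the control/intervention groups, socio-demographic factors and other confounding variables will be included in the GEE models".
- **Primary outcome** (same section). "The primary outcome measure is levels of unmet needs as measured by the SCNS-P&C". No time point or contrast is attached to it.
- **Surveys** (Outcome measures). "A CATI survey will be conducted with caregivers at baseline (t0), one month (t1), three months (t2) and six months (t3". Baseline is thus one of four measurements of the same outcome.
- **Timing of t0** (Procedure). "Baseline CATIs occur before the intervention group caregivers consult the GP".
- **Power** (Sample size and statistical analysis). The calculation rests on "utilising the standard deviations for each of the domains for the patient version of the SCNS [30-32] (between 15 to 24" and on "using a 5% significance level, having a minimum of 200 caregivers in each of the two comparison groups". It gives 80% power for differences of 4.2 to 6.7 per domain.

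The baseline score, visit and group-by-visit are not named. The text does not say that the listed terms are the only ones.

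**The concern.** The intervention cannot have acted through the GP consultation at t0, so the expected group difference there is zero. A single group coefficient fitted to all four waves averages that zero with the three follow-up differences and understates the effect. If t0 is dropped instead, the estimate is not diluted, but an early measurement of the same score, normally a strong predictor of later values, goes unused. As described, the model does not show which of these applies or which coefficient is the treatment effect.

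Baseline adjustment matters somewhat more here than in a fully randomised trial. The Randomization section assigns later caregivers of a participating GP to that GP's existing arm. With about 330 GPs for 520 caregivers, up to 520 − 330 = 190 caregivers (190/520 = 37%) could be allocated this way, so chance balance on baseline need is less assured.

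**Working it through.** **Inputs from the article:** SD 15 to 24; detectable differences 4.2 to 6.7; 200 completers per arm; 5% significance level (two-sided reproduces the figures); 80% power; surveys at t0, 1, 3 and 6 months.

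**Assumed:** exchangeable within-caregiver correlation r, not given, shown from 0.3 to 0.8; equal SD at each wave; complete data; a constant effect at t1 to t3; no allowance for GP clustering.

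**1. The plan's own figure.** Detectable difference = (1.960 + 0.842) × SD × √(2/200) = 0.280 × SD, which is 4.20 for SD 15 and 6.72 for SD 24. Power at 200 per arm is 0.800 (4.2, SD 15) and 0.797 (6.7, SD 24). The stated figures reproduce, as a comparison of two means at one occasion without baseline adjustment.

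**2. Dilution if t0 is a response and group is a main effect only.** Expected coefficient = (0 + d + d + d)/4 = 0.75d. So 0.75 × 4.2 = 3.15 and 0.75 × 6.7 = 5.03. If the effect varies over follow-up, the coefficient is still 0.75 of its mean over the three visits. With attrition, assuming 520, 480, 440 and 400 respondents at the four waves and an independence working correlation, the factor is 1320/1840 = 0.72.

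**3. Power.** Variance factors, in units of SD²:

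- four-wave mean: (1 + 3r)/4
- three follow-ups, baseline ignored: (1 + 2r)/3
- three follow-ups, adjusted for baseline: (1 + 2r)/3 − r²

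SE = √(2/200 × factor) in SD units; power = Φ(effect/SE − 1.960). The effect is 4.2/15 = 0.28 SD, or 0.75 × 0.28 = 0.21 SD for the four-wave main effect.

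Example at r = 0.5:

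- Four waves: factor 0.625, SE 0.0791, 0.21/0.0791 = 2.66, power 75.7%.
- Follow-ups only: factor 0.667, SE 0.0816, 0.28/0.0816 = 3.43, power 92.9%.
- Follow-ups with baseline: factor 0.417, SE 0.0645, 0.28/0.0645 = 4.34, power 99.1%.

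| r | t0 a response, group main effect | t1–t3, baseline unused | t1–t3, baseline as covariate | SE ratio, adjusted to unadjusted |
|---|---|---|---|---|
| 0.3 | 86.1% | 97.0% | 98.8% | 0.91 |
| 0.4 | 80.8% | 95.1% | 98.8% | 0.86 |
| 0.5 | 75.7% | 92.9% | 99.1% | 0.79 |
| 0.6 | 70.9% | 90.5% | 99.6% | 0.71 |
| 0.7 | 66.5% | 87.9% | 99.9% | 0.62 |
| 0.8 | 62.5% | 85.3% | >99.9% | 0.51 |

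The last column is √[((1 + 2r)/3 − r²) / ((1 + 2r)/3)]. With 6.7 and SD 24, the powers are at most 0.3 percentage points lower.

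**4. Where the diluted model falls below 80%.** It matches the single-occasion test when (1 + 3r)/4 = 0.75² = 0.5625, so r = (4 × 0.5625 − 1)/3 = 0.42. Below that, averaging over waves offsets the dilution in power, though not in the estimate.

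**5. Visit main effects alone.** With complete data, group and visit are orthogonal, so adding visit leaves the group coefficient unchanged. A rough simulation (260 per arm, dropout, true effect 6.7) agrees. The coefficient averaged 3.73 with and without visit at r = 0.5, and 4.26 and 4.25 at r = 0.7. A post-baseline-by-group term gave 6.31 and 6.78. At 40 replicates this shows the pattern but does not size the dilution.

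**The case against.** The strongest reply is that the article does not commit to the faulty model. It lists terms that will be included and does not call the list complete. It describes an analysis over time. Its open class of other confounders could hold the baseline score, all the more because later caregivers of a GP are not individually randomised. No section says that t0 is a response row. The exact mean model and primary contrast are commonly left by a condensed article to a full protocol or SAP, which is not shown. All of this stands. A reader might infer that the primary estimate will be understated; the documents do not support that, because dilution needs both t0 as a response and no term separating baseline from follow-up, and neither is fixed.

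The size is also conditional. At correlations of about 0.4 or below, even the diluted model meets the stated 80%. The 99% for the adjusted model assumes an effect constant from month 1, whereas the Procedure section schedules a second needs assessment at 3 months and the Discussion suggests that the impact may become clearer over six months.

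A second tempting inference starts from the remark that GEE works by "reflecting the relationship between the longitudinal development of the dependent variable and the longitudinal development of the independent variables over time": that the trial will adjust for coping or HADS measured after allocation. The remark is a general description of the method. Outcome measures lists anxiety, depression and coping style as outcomes, and nothing proposes them as covariates. That inference is not supported.

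What remains is that the stated list omits the most useful covariate already collected, and does not identify the treatment coefficient or the role of t0.

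**Conclusion.** The point holds as an improvement to make, not as a demonstrated error. Under the least favourable reading, the effect shrinks to about 0.75 of its post-baseline value, and power drops below 80% above a correlation of about 0.42. If t0 is simply left out, there is no dilution and power is 85% to 97% over correlations 0.8 to 0.3. Using the baseline score would then still cut the standard error by 9% to 49%. The dilution factor follows from the design with complete data; the power and precision figures rest on the assumed exchangeable correlation, constant effect and negligible GP clustering. Under either use of t0, adjusting for the baseline score and taking the effect from post-baseline visits does better than the terms named.

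**What to change.** State the primary model in full. Take t1, t2 and t3 as responses, with the baseline value of the same SCNS-P&C score as a covariate, plus visit, group and group-by-visit, and the socio-demographic terms already planned. Equivalently, keep all four waves with a common baseline mean for the two arms and a post-baseline-by-group term. Do not rely on visit main effects alone.

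Name one post-baseline contrast as the primary treatment effect, for example the group difference averaged over 1, 3 and 6 months, or the difference at a single named visit. The choice should reflect when the effect is expected.

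If an existing SAP already specifies this, a one-sentence cross-reference is enough. The cost is analysis wording only, since t0 is already collected from every participant; no new data, visits or sample size are needed.
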